### Ethics

The present study was approved by the Medical Ethics Committee of Arnhem-Nijmegen (NL68540.091.19) and is registered within the Netherlands Trial Registry (NL7628). All participants will give written informed consent according to the Declaration of Helsinki before entering the study and will be explicitly informed that they can withdraw from participation at any time without any further explanation. Participants will be given an identification code, which will be used for further data acquisition. Participant names with their identification codes will be kept securely and only accessible by the principal investigator and coordinating researcher. A trained and independent monitor will be assigned to monitor the research process, which includes monitoring the completeness of informed consent, data safety, and correspondence with the ethics committee. Although these are not expected to occur, serious adverse events will be reported to the Medical Ethics Committee.

### Randomization

Participants will be randomly assigned to either the rTMS or medication arm. Randomization will be done via Castor EDC and will be stratified for treatment center, total number of depressive episodes, and current depression severity (moderate: HDRS-17 score of 17–23; severe: HDRS-17 score of > 23). Castor EDC randomizes participants with a four and six block design. More information about the randomization algorithm can be found on Castor’s website (https://helpdesk.castoredc.com/article/50-the-randomizationalgorithm-in-castor).

### Interventions

#### rTMS

rTMS treatment will be performed using a Magstim Rapid 2 (Radboudumc) or a Deymed DuoMag XT-35 or XT-100 equipment (neurocare and ETZ) using generic figure-8 coils). All rTMS parameters used in the proposed study are within the range considered safe according to the latest published safety guidelines [34, 35]. Firstly, the resting motor threshold (rMT) will be defined in each participant as the minimal stimulation intensity evoking an MEP of ≥0.05 mV in 50% of the trials in the muscle of the right thumb (M. abductor pollicis brevis). Note that rMT will be determined at the beginning of every week before the first treatment session. We will use BeamF3 (freely available software at (http://clinicalresearcher.org/F3/calculate.php) to find the DLPFC, which is based on electrode position F3 from the EEG 10–20 system [36]. A detailed description of this method can be found in Beam et al., (2009) [36]. The coil will be positioned over this location at an angle of 45° relative to the midline.

rTMS will be conducted using a high-frequent protocol, applying 60 trains of 10 Hz pulses with a duration of 5 s and an inter-train interval of 25 s over the left DLPFC (50 pulses per train, 3000 pulses per session), with an intensity of 120% of the rMT. Twenty-five rTMS sessions will be given over the course of 8 weeks, following a schema of 4, 4, 4, 3, 3, 3, 2, 2 sessions per week. After a minimum of fifteen sessions (corresponding to 4 weeks), treatment may be ended. This is only possible when the scores on the HDRS-17 decrease to a minimum of symptoms (score < 8, in remission) for at least two measurements in a row. However, when the scores still show a decline, the patient is still improving and will likely progress even further. The rTMS sessions should be continued until the patient’s HDRS scores remain below 8 for two measurements in a row but no longer than 8 weeks (given the set-up of the approved ZonMW grant). Table 1 shows an overview of the rTMS treatments and measurements during the eight-week treatment period. Patients responding to rTMS are allowed to receive booster sessions in case of relapse.

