Despite being approved as a treatment for patients with TRD, the exact position of rTMS in the treatment algorithms of depression remains unclear. The biological steps within these algorithms usually follow a stepped-care approach, starting with multiple, subsequent psychopharmacological steps and ECT as the last step. Not much is known about the comparative efficacy of rTMS to other biological steps, although studies have compared rTMS to venlafaxine and ECT [23, 24]. Importantly, the efficacy of these biological treatments may also depend on the level of treatment resistance. It is therefore difficult for the treating physician to decide when rTMS should be considered as a treatment option for his or her patient. A few studies have performed economic evaluations, comparing rTMS to other antidepressant treatments. Results on the cost-effectiveness of rTMS compared to ECT show mixed results, with some studies suggesting rTMS and others ECT as the most cost-effective treatment [25–28], where the level of treatment resistance and severity of depression may be the crucial factor. When compared to antidepressant medication, rTMS resulted in slightly more quality of life at lower costs [29, 30]. However, no studies have assessed the cost-effectiveness of rTMS as a follow-up step in patients with moderate level of treatment resistance.

Therefore, we want to examine the comparative efficacy of rTMS combined with CBT as an alternative to the current next pharmacological steps (i.e., switch or augmentation of antidepressant) in a randomized controlled trial. We propose to investigate the effectiveness of rTMS in combination with CBT and continued antidepressant medication compared to the next step in the treatment algorithm, in a sample of patients with non-psychotic unipolar depression, who did not respond to two adequate antidepressant treatments. We aim at testing the effectiveness of both treatments in terms of clinical improvement and the prevention of recurrence over the course of 6 months, as well as the cost-effectiveness. Furthermore, we will examine effect decay or preservation up until 12 months. We also aim to explore the effects of the two treatments on specific symptoms associated with depression, such as anhedonia, anxiety, rumination, cognitive reactivity, and sleep. Finally, we aim to assess the effect of expectations regarding the treatment on its effectiveness.

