### Evaluation of treatment response and remission

One of our secondary outcomes is treatment response (50% reduction in HDRS-17 score) and remission (≤7 on HDRS-17) at 8 weeks, and 4 and 6 months. For a subgroup of patients, this data will also be available for 9 and 12 months, as part of the extended follow-up. For each treatment condition, the percentage of participants that responds or is in remission will be calculated, for each time point. Kaplan Meier survival estimates will be calculated based on outcome after the eight-week treatment period and during follow-up. Scores will be compared using Cox regression analysis to take into account both the rate of response or remission and the time needed to reach response or remission.

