### Strengths and limitations

This study has several strengths. Firstly, since this RCT takes place in a naturalistic clinical care setting, translation of our results to clinical practice will be easier. Regardless of the outcome of this trial, the results can inform clinical decision making and aid in choosing the right treatment for a patient. Another strength lies in the duration of the follow-up, which is longer than previous rTMS trials. Since information up until a year after start of the treatment becomes available, we can also say something about the durability of treatment effects on the longer term and the cost-effectiveness of the intervention over a longer course.

Despite these strengths, some limitations should be considered. First, patients receive medication and CBT as usual care in accordance with the Dutch guidelines. While this reflects clinical practice, treatment heterogeneity is expected, as different psychological and/or pharmacological interventions are provided in different dosages and in varying formats across the participating institutes. Nevertheless, due to the randomized design, the heterogeneity should be similar across conditions.

Another limitation may be that rTMS might lead to improvements in depressive symptoms due to non-specific therapy effects such as more attention by a clinician and a more active lifestyle due to the large number of hospital appointments. A solution would be to use a sham condition, with which these non-specific therapy effects can be assessed, however, the effects of sham protocols have been researched extensively and show that these effects are minimal [49, 50]. As this is a pragmatic trial that aims to assess the comparative efficacy of rTMS and current antidepressant treatments a sham condition would have no added value. Furthermore, non-specific therapy effects can also be expected in the medication group, as these patients will also have more appointments than usual due to the research assessments.

Thirdly, because patients ultimately decide whether they want to participate, there might be a selection bias. Treatment with rTMS especially is time-consuming and intensive, potentially resulting in a selection of highly motivated patients. Importantly, even if rTMS attracts a certain patient population, it can be an effective treatment for depression, not limiting the additional value of this study in examining a (cost-)effective treatment alternative for depression.

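### With booster rTMS permitted on relapse, response and remission percentages at 4 to 12 months describe rTMS with boosters, and the stated follow-up analyses do not measure recurrence or decay after the 8-week course

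*Protocol article*

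**What the plan says.** All references are to the protocol article.

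- **Booster rule (Interventions, rTMS).** "Patients responding to rTMS are allowed to receive booster sessions in case of relapse". No time limit is given.
- **Aims (Background).** The two treatments are to be tested for "clinical improvement and the prevention of recurrence over the course of 6 months", and the next sentence adds: "Furthermore, we will examine effect decay or preservation up until 12 months". Study design and Discussion repeat the decay aim. Strengths and limitations claims of the long follow-up that "we can also say something about the durability of treatment effects on the longer term".
- **Follow-up analysis (Evaluation of treatment response and remission).** For each arm, "the percentage of participants that responds or is in remission will be calculated, for each time point", at 8 weeks, 4 months and 6 months. Then: "For a subgroup of patients, this data will also be available for 9 and 12 months, as part of the extended follow-up". Kaplan-Meier estimates and Cox regression are added "to take into account both the rate of response or remission and the time needed to reach response or remission".
- **Relapse assessment (Primary objective - depressive symptoms).** The SCID is given at baseline, 6 and 12 months, partly to detect relapses and recurrences.
- **Later rTMS in the other arm (Study design).** Medication patients who have not recovered may receive rTMS once the 8 weeks are over.
- **Primary outcome (Change in depression severity).** HDRS-17 over the 8 treatment weeks only.

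**The concern.** In the rTMS arm, loss of effect is the trigger for the treatment meant to restore it, and restoration can occur before the next scheduled visit. A percentage in remission at that visit then mixes two groups: patients who stayed well after the initial course, and patients who relapsed and were treated again. Both are legitimate outcomes of care, but only the first is preservation of the effect of the 8-week course.

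The survival analysis does not separate them. Its event is reaching response or remission, so a patient who reached it by week 8 has already had the event and contributes nothing on whether it was later lost.

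At stake is the durability statement. The trial is meant to inform where rTMS belongs in treatment guidelines, and a reader could credit the initial course with durability that partly reflects repeated treatment. The cost-effectiveness end-term, remission at 6 months, has the same composition and needs the same label.

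**Working it through.** **1. The plan's own figure.** The sample size section gives d = 0.33, two-sided alpha 0.05, power 0.80, five post-baseline measurements, and correlations of 0.59 (baseline with follow-up) and 0.69 (between follow-ups).

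- Variance factor for repeated-measures ANCOVA: (1 + 4 × 0.69)/5 − 0.59² = 0.752 − 0.3481 = 0.4039.
- n per arm = 2 × (1.960 + 0.842)² × 0.4039 / 0.33² = 58.2, so 59.
- With 10% loss: 59/0.90 = 65.6, so 66 per arm and 132 in total.

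This reproduces the article. It rests on the 8-week HDRS-17 outcome, which ends before the follow-up visits concerned, so nothing below changes it. It supplies the 66 used in step 3.

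**2. One patient through the stated analyses.** Take an rTMS patient with HDRS-17 below 8 at week 8 who relapses in month 3, is boosted, and scores below 8 at month 6.

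| Analysis | What it records |
|---|---|
| Percentage in remission at week 8 and month 6 | Remitter at both |
| Kaplan-Meier/Cox, time to remission | Event by week 8; the relapse is not seen |
| SCID at 6 months | Can identify the relapse, but none of the analyses described in the article uses it |

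**3. Size.** Let p be the fraction in remission at week 8, b the fraction of those who relapse and are boosted, and c the fraction of the boosted who are in remission again at the visit.

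- Overstatement of preserved remission among remitters = b × c.
- Overstatement of the arm's remission percentage, all rTMS patients as denominator = p × b × c.

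The documents give neither b nor c. For p, the Background cites 56% from a naturalistic rTMS-plus-CBT study. Illustration with assumed b = 0.30 and c = 0.60:

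- Remitters: 66 × 0.56 = 37.0. Boosted: 37.0 × 0.30 = 11.1. Recaptured: 11.1 × 0.60 = 6.7.
- Among remitters: 70% preserved without recaptures, 88% with them, a shift of 18 points.
- Among all 66: 0.56 × 0.70 = 39.2% against 0.56 × 0.88 = 49.3%, a shift of about 10 points.

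Assumed ranges b = 0.15 to 0.45 and c = 0.40 to 0.80 give 6 to 36 points among remitters, and 0.56 × 6 = 3.4 to 0.56 × 36 = 20.2 points among all 66.

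The same product for response, all 66 as denominator, with 30-60% responding, 10-40% of responders relapsing and boosted, and 30-80% of those recaptured, gives 0.9 to 19.2 points. The mid-case is 0.45 × 0.25 × 0.50 = 5.6 points (33.8% becomes 39.4%).

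All these figures assume that no relapser would have been well at that visit without a booster. They are therefore upper values for the rates chosen.

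**4. The other arm.** If 50-87% of medication patients do not recover, 25-80% of those receive rTMS after week 8 and 20-56% of those gain remission (assumed ranges), that arm rises by 0.50 × 0.25 × 0.20 = 2.5 points to 0.87 × 0.80 × 0.56 = 39 points. Later treatment can therefore raise both arms.

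**The case against.** The strongest case on the other side has four parts.

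*The strategy is a legitimate target.* The trial is pragmatic and analysed primarily by intention to treat, and the booster rule is disclosed. The as-observed percentages validly compare strategies that include permitted later treatment. This stands, and those percentages should stay. What they cannot isolate is decay after the initial course.

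*Recurrence is recoverable.* Relapse precedes a booster, and the SCID is scheduled separately at 6 and 12 months. This stands too. A reader might infer that the trial cannot answer the recurrence aim at all. The documents do not support that, because the data to count relapse are planned. The gap lies in the analysis stated for them.

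*A condensed article may leave handling to an analysis plan.* This holds for silence, so the absence of a rule for visits after a booster is no finding by itself. But the article does state its follow-up analyses, and they target gaining response or remission, whereas the aims concern losing it.

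*The aim is peripheral.* Aims and hypotheses lists neither recurrence nor decay as an objective. This limits the weight of the point. The aims are nevertheless stated in Background, Study design and Discussion, and Strengths and limitations relies on them.

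A reader might also infer that boosters tilt the comparison between arms towards rTMS. The documents do not support that either. Medication patients may receive rTMS after week 8, so the net effect on the contrast has no fixed sign.

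**Conclusion.** The point holds for the rTMS arm's own course after week 8. Response and remission percentages at 4 to 12 months describe rTMS with boosters as permitted, and no stated clinical analysis has loss of response, loss of remission or relapse as its event. Within that arm, successful boosters can shift apparent durability only upwards.

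The size cannot be derived from the documents. It equals the boosted fraction times the recaptured fraction among remitters, and is smaller when all rTMS patients are the denominator. The 18-point and 10-point figures rest on assumed relapse and recapture rates. The 56% comes from a study that gave CBT during every rTMS session, and the article itself says its own CBT differs and could yield different outcomes. They show that the effect could matter; they do not estimate it.

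The primary analysis and the sample size are untouched. This merits a change to the follow-up analysis and to how durability is described; it is no objection to the trial's main comparison.

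**What to change.** These are analysis changes only. No change to who receives boosters, or to any other treatment rule, is proposed.

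1. Keep the as-observed intention-to-treat percentages, and label them as outcomes of each strategy including permitted later treatment.
2. Beside them, add a time-to-loss analysis among week-8 responders and, separately, week-8 remitters. Report the percentage preserved at 4, 6, 9 and 12 months.
3. Use one event definition in both arms: the first of (a) SCID-confirmed relapse, (b) loss of response or remission on the HDRS-17 at a visit, or (c) the start of any new antidepressant treatment after week 8. Component (c) covers booster rTMS, rTMS given to medication patients after week 8, and a new medication step in either arm. Counting boosters alone would penalise only the rTMS arm.
4. Base (c) on recorded start dates. The article does not say whether booster dates are captured; if they are not, add a dated field in Castor EDC.
5. State that this comparison is restricted to week-8 responders or remitters, a group defined after randomisation, and is therefore descriptive rather than fully randomised.

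The cost is some analysis wording, modest extra work and possibly one data field. The reported durability of rTMS is likely to look less favourable than the as-observed figure.

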#### CBT

All patients will receive sessions of cognitive behavioral therapy, either in a group or individually, and at least once a week. This may differ between patients, as it would during usual care. Information on the form and frequency of CBT will be recorded in Castor EDC.

#### Medication

Treatment as usual will consist of protocolled pharmacological treatment steps that are prescribed within the medication algorithm of the Dutch guideline. This will consist of either a switch from the current antidepressant medication to a tricyclic antidepressant (TCA) or augmentation of the current antidepressant medication with lithium or a second generation antipsychotic [37]. Information on the type, dose and duration of medication will be recorded in Castor EDC.

#### Measures

See Fig. 2 for a schedule of the assessments.

**Fig. 2 Fig2:**
[figure not shown]
Assessment schedule

### Primary objective - depressive symptoms

Section A, B and D of the Structured Clinical Interview for DSM 5 disorders (SCID-I; 2018) will be used at baseline and after six and 12 months to assess depressive episodes and possible relapses/recurrences at follow up and extended follow-up. During intake, the SCID will also be used to assess presence of bipolar disorder or psychotic features. The SCID takes about 20 min to complete.

The Hamilton Depression Rating Scale 17 item version is an observer rated scale used to assess the severity of depressive symptoms (HDRS-17) [38]. The HDRS-17 is assessed during screening, treatment, follow-up and extended follow-up. Completion takes approximately 15 min. During the eight-week treatment period, the HDRS-17 will be administered every five rTMS treatments, and on corresponding days for participants in the medication arm. See Fig. 2 for the schedule during treatment. Response is defined as a ≥ 50% reduction in score on the HDRS-17, whereas remission is defined as a score of < 8. Response and remission will be determined after 8 weeks of treatment and at the final follow-up assessment of the RCT at 6 months after baseline.

The Beck Depression Inventory will be used in order to measure individual differences in depressive symptoms (BDI-II) [39]. Participants will be asked to fill in the BDI-II once every five rTMS sessions or on corresponding days when they are in the medication arm. See Fig. 2 for the schedule during treatment. Participants have to indicate on 21 items in how far these items describe themselves on a scale ranging from 0 to 3 resulting in a sum score between 0 and 63. The total score can further be divided into four ranges, describing the severity of depressive symptoms from minimal (0–13), mild (14-19), moderate (20-28) to serious depressive symptoms (29–63). Completion takes about 5 min.

Two questionnaires will be used to assess and quantify the level of treatment resistance. The Dutch Measure for quantification of Treatment Resistance in Depression (DM-TRD) quantifies treatment-resistant depression by assessing treatments in the depressive episode as well as functional impairment, comorbid anxiety, personality disorders and psychosocial stressors [40]. The DM-TRD generally takes 10-20 min to complete after the diagnostic interview. The Antidepressant Treatment History Form (ATHF) can be administered in 10 min or less, depending on the number of antidepressant trials of a patient [41].

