### Participants

We aim to include 132 adult patients diagnosed with moderate to severe (HDRS > 16) unipolar MDD without psychotic symptoms, with failed response to at least two treatment trials with adequately dosed antidepressants and a current episode of less than 2 years. Exclusion criteria are: lifetime diagnosis of bipolar disorder, schizophrenia or schizoaffective disorder; current diagnosis of substance abuse disorder or organic brain syndrome; the presence of a concurrent significant medical condition impeding the ability to participate; previous treatment with rTMS or ECT; epilepsy, convulsion or seizure; serious head trauma or brain surgery; large or ferromagnetic metal parts in the head (except for a dental wire); implanted cardiac pacemaker or neurostimulator; or pregnancy. A subset of 92 patients will be part of the extended follow-up up to 12 months.

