### Sample size calculation

The sample size calculation is based on the outcome of the rTMS arm in comparison to the medication arm. To flag up a clinically significant difference between rTMS and medication, we took an effect size of d = 0.33, which corresponds to the lower boundary of a medium clinically meaningful effect [31] and is similar to effect sizes for research on antidepressant medication [32]. Alpha will be set at 0.05, with a power (1-beta) of 0.80. We will employ a two-sided repeated measures ANCOVA, with a total of six repeated measurements (baseline and measurements corresponding to rTMS treatment 5, 10, 15, 20, and 25). See also Table 1 for an overview and timepoints of the measurements. Based on HDRS-17 data from one of our previous studies, we expect the correlation between baseline and follow-up to be *r* = 0.59, and the correlation between follow-up measurements to be *r* = 0.69. The sample size calculation was performed in STATA version 15.1 and resulted in an estimated required sample size of 59 participants per condition. Compensating for possibly 10% loss to follow-up, the total sample size at baseline will be increased to 132 participants.

**Table 1 Tab1:** Overview of rTMS sessions and measurements during the treatment period. For participants in the medication arm, measurements will be done on days corresponding to treatment day 5, 10, 15, 20, and 25 of rTMS treatment

	Week 1					Week 2					Week 3					Week 4				
Day	1	2	3	4	5	1	2	3	4	5	1	2	3	4	5	1	2	3	4	5
rTMS	x	x		x	x	x	x		x	x	x	x		x	x	x		x		x
HDRS						x						x								x
BDI-II						x						x								x
	Week 5					Week 6					Week 7					Week 8				
Day	1	2	3	4	5	1	2	3	4	5	1	2	3	4	5	1	2	3	4	5
rTMS	x		x		x	x		x		x		x		x			x		x	
HDRS								x											x	
BDI-II								x											x	

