### Change in depression severity

Our primary outcome during the intervention is overall change in HDRS-17 depressive symptom severity during 8 weeks of treatment by condition (rTMS versus medication). Data will be collected at 6 timepoints: at baseline, and after 5, 10, 15, 20, and 25 rTMS treatment sessions (or corresponding days for participants in the medication arm). We will employ linear mixed modelling using marginal means, with HDRS-17 score as our dependent variable and treatment (rTMS or medication) as independent variable. Age and gender will be added as covariates, since these have been shown to affect the phenomenology of depression.

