### Clinical implications

With our results, we aim to inform clinical decision making. Currently, rTMS does not have a clear position in the treatment algorithm of guidelines for depression. Though many clinical trials have established rTMS as a safe and effective treatment option for depression, head-to-head comparisons are scarce. Despite its potential as a mainstream treatment for depression, the placement of rTMS in the treatment algorithm is limited by the lack of comparative results, in particular taking its value in combination with CBT into account. The results of this trial will inform us whether rTMS should be considered as treatment alternative to antidepressant medication in patients who have not responded to two previous treatment steps and will give important directions about the proper place of rTMS in treatment guidelines.

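### The primary model names only age and gender as covariates, leaving out the stratification factors and the collected treatment-resistance score; this costs some precision but causes no bias

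*Protocol article*

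**What the plan says.** Five places in the protocol article bear on this point.

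- **Primary objective - depressive symptoms:** "Two questionnaires will be used to assess and quantify the level of treatment resistance". These are the DM-TRD, which also scores functional impairment, comorbid anxiety, personality disorders and psychosocial stressors, and the ATHF. None of the analysis sections mentions either instrument again.
- **Background:** "the efficacy of these biological treatments may also depend on the level of treatment resistance".
- **Randomization:** allocation is stratified by centre, total number of depressive episodes and HDRS-17 severity (17 to 23, or above 23). Treatment resistance is not a stratification factor.
- **Change in depression severity:** the primary analysis is a linear mixed model of HDRS-17 on treatment, with data at baseline and five later points. "Age and gender will be added as covariates", on the ground that both influence how depression presents itself. The stratification factors are not named.
- **Sample size calculation:** "We will employ a two-sided repeated measures ANCOVA, with a total of six repeated measurements", counting baseline as one of the six.

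On the population, Participants admits patients "with failed response to at least two treatment trials with adequately dosed antidepressants" and states no upper limit. Clinical implications frames the conclusion for use "in patients who have not responded to two previous treatment steps". Background likewise refers to two adequate treatments, and both Background and the opening of the Discussion speak of moderate resistance.

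**The concern.** A covariate earns its place in the primary model by predicting the outcome, or by having been used to restrict the randomisation. The reason given for age and gender concerns how depression presents, which is not the same as predicting HDRS-17 over eight weeks. The variables with a better claim on the article's own terms are the three stratification factors and the resistance score, and the article names none of them.

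The stake is efficiency. If the omitted variables are prognostic, the standard error of the treatment effect is larger than it needs to be, in a trial sized with almost no margin above 80% power. When factors used to stratify the randomisation are left out of the analysis, the usual standard errors also tend to be too wide.

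A smaller matter is interpretation. The conclusions are worded for a narrower group than the eligibility criteria admit.

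**Working it through.** **1. Inputs, all from Sample size calculation.** "we took an effect size of d = 0.33"; "Alpha will be set at 0.05, with a power (1-beta) of 0.80"; two-sided test; one baseline and five post-baseline measurements; correlation 0.59 between baseline and follow-up and 0.69 among follow-up measurements; 10% loss to follow-up.

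**2. Reproducing the plan's figure.** The variance of the mean of five post-baseline scores, adjusted for baseline and in units of the HDRS-17 variance, is

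(1 + 4 × 0.69)/5 − 0.59² = 0.752 − 0.3481 = 0.4039.

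Per arm, n = 2 × (1.960 + 0.842)² × 0.4039 / 0.33² = 58.2, rounded up to 59. Two arms give 118, and 118/0.90 = 131.1, rounded up to 132. Both stated figures reproduce. Power at 59 per arm is 80.5%.

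This calculation credits adjustment for baseline HDRS-17 but for no other covariate. Leaving out resistance and the other stratification factors therefore contradicts no stated figure.

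**3. What a resistance covariate could add.** The documents give no predictive strength for the DM-TRD, so the share R of residual variance that it explains is an assumption. The variance becomes 0.4039 × (1 − R), and the equivalent total sample without the covariate is 132/(1 − R).

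| R (assumed) | Variance | n per arm for 80% power | Power at 59 per arm | Equivalent total |
|---|---|---|---|---|
| 0 | 0.4039 | 59 | 80.5% | 132 |
| 0.02 | 0.3958 | 58 | 81.3% | 134.7 |
| 0.04 | 0.3877 | 56 | 82.1% | 137.5 |
| 0.09 | 0.3675 | 53 | 84.1% | 145.1 |
| 0.16 | 0.3393 | 49 | 86.8% | 157.1 |

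R = 0.04 and 0.16 correspond to partial correlations of 0.2 and 0.4 with the outcome, given baseline. R = 0 is included because nothing in the article rules it out.

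**4. Stratification factors.** The same formula applies to whatever centre and number of episodes explain, for which the article also gives no figure. The severity stratum is a two-level version of baseline HDRS-17. Once the continuous score is in the model, whose squared correlation of 0.3481 is already credited in step 2, the stratum can be expected to add little further precision.

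**5. Effect modification.** A main-effect covariate does not show whether the treatment effect varies with resistance; that needs an interaction. For a binary split with proportion p in one group and 59 per arm, the standard error is √[0.4039 × (2/(59p) + 2/(59(1 − p)))]. This is 0.234 at p = 0.5 and 0.255 at p = 0.3. Power for an interaction of 0.33 SD is then 29% and 25%, and the interaction detectable with 80% power is 0.66 and 0.72 SD.

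**6. Population wording.** Eligibility is two or more failed trials. The aim and the clinical implications say two, and the Background and Discussion say moderate. The article itself describes staging schemes based on the number of failed trials and a division into moderate and severe resistance, so moderate carries meaning here. No entry criterion restricts the sample to it by number of failed trials. The exclusion of previous rTMS or ECT and the two-year limit on the current episode restrict it only indirectly.

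**The case against.** The strongest reply is that covariate choice is a matter of judgement. Age and gender are named in advance with a reason, randomisation protects the comparison, and no stated figure fails. The gain rests on an assumed correlation and could be nil. All of that stands, and it is why the point is minor. It does not remove the point, because the article is not silent on covariates: it names a list, and that list omits the variables used to stratify the randomisation.

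Four stronger readings are tempting, and the documents do not support them.

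- **That the article calls resistance a likely driver of effect.** It says only that efficacy may depend on it. Its remark that resistance and severity may be the crucial factor concerns mixed cost-effectiveness results against ECT, which is not a comparator here.
- **That the plan wrongly lacks an analysis by resistance level, so that the trial cannot support its conclusion.** Such an analysis may sit in the full protocol or SAP, which are not shown, and it would be underpowered. The trial estimates an average effect in the patients enrolled, all of whom have failed at least two trials. Clinical implications, read literally, covers patients with more failures too. Only the label of moderate resistance is hard to reconcile with the entry criteria.
- **That baseline HDRS-17 is ignored.** Without any baseline information the variance would be 0.752 and power at 59 per arm 54%. But the analysis section lists baseline among its six time points, and a mixed model with baseline among the outcomes can carry that information.
- **That the DM-TRD is certainly a baseline measure.** The text places it after the diagnostic interview, but that interview is held at baseline and again at six and 12 months. The assessment schedule is in a figure that is not shown.

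**Conclusion.** The point holds as a minor, inexpensive improvement to the primary analysis. The primary comparison is unbiased as planned, and the sample size stands at 59 per arm and 132 in total. The named covariates give up whatever precision the stratification factors and the DM-TRD would provide. For the DM-TRD alone, power moves from 80.5% to at most about 87%, on the assumption that it explains no more than 16% of residual variance; at 2% it reaches only 81.3%. These figures also rest on the plan's own correlations and effect size, and on the score being taken at baseline. The mismatch in population wording is secondary and affects interpretation only.

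**What to change.** In Change in depression severity:

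- Add the stratification factors (centre, number of depressive episodes, severity) as covariates.
- Add the DM-TRD score, provided that it is taken at baseline, and state that timing.
- Enter continuous baseline HDRS-17 as a covariate and keep only the five post-baseline scores as outcomes. This matches the ANCOVA used for the sample size, and baseline is then not both outcome and covariate.

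In Background, the opening of the Discussion and Clinical implications, describe the population as in Participants, that is, two or more failed trials. Report the distribution of resistance in the table of participant characteristics and limit the conclusions accordingly. A treatment-by-resistance interaction is optional; if included, it should be labelled exploratory and underpowered.

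The cost is a change of wording and some degrees of freedom: one for the DM-TRD, one for severity, at least one for number of episodes, and five for centre if centre means the six named organisations. No new data, visits or patients are needed.
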